## Abstract

**Background:**

Very few Australian infants are exclusively breastfed to 6 months as recommended by the World Health Organization. There is strong empirical evidence that fathers have a major impact on their partner’s decision to breastfeed and continuation of breastfeeding. Fathers want to participate in the breastfeeding decision making process and to know how they can support their partner to achieve their breastfeeding goals. The aim of the Parent Infant Feeding Initiative (PIFI) is to evaluate the effect on duration of any and exclusive breastfeeding of three breastfeeding promotion interventions of differing intensity and duration, targeted at couples but channelled through the male partner. The study will also undertake a cost-effectiveness evaluation of the interventions.

**Methods/design:**

The PIFI study is a factorial randomised controlled trial. Participants will be mothers and their male partners attending antenatal classes at selected public and private hospitals with maternity departments in Perth, Western Australia. Fathers will be randomly allocated to either the usual care control group *(CG)*, one of two medium intensity (*MI1* and *MI2*) interventions, or a high intensity (*HI*) intervention. *MI1* will include a specialised antenatal breastfeeding education session for fathers with supporting print materials. *MI2* will involve the delivery of an antenatal and postnatal social support intervention delivered via a smartphone application and *HI* will include both the specialised antenatal class and the social support intervention. Outcome data will be collected from couples at baseline and at six and 26 weeks postnatally. A total of 1600 couples will be recruited. This takes into account a 25 % attrition rate, and will detect at least a 10 % difference in the proportion of mothers breastfeeding between any two of the groups at 26 weeks at 80 % power and 5 % level of significance, using a Log-rank survival test. Multivariable survival and logistic regression analyses will be used to assess the effect of the treatment groups on the outcomes after adjusting for covariates.

**Discussion:**

The PIFI study will be the first Australian study to provide Level II evidence of the impact on breastfeeding duration of a comprehensive, multi-level, male-partner-focused breastfeeding intervention. Unique features of the intervention include its large sample size, delivery of two of the interventions by mobile device technology, a rigorous assessment of intervention fidelity and a cost-effectiveness evaluation.

**Trial registration:**

Australian New Zealand Clinical Trials Registry ACTRN12614000605695. Registered 6 June 2014

## Background

Breastfeeding is a cornerstone of both short- and long-term health [1, 2]. There are nutritional, immunological and psychological dose-related benefits for the child and as such exclusive breastfeeding can provide the greatest gains for infant development and some protection against childhood obesity and chronic disease in adult life [1–4]. Health benefits for the mother include lactational amenorrhoea, protection against ovarian and premenopausal breast cancers, bone remineralisation to levels exceeding those present before lactation and improved blood glucose profiles in women with gestational diabetes [5]. The World Health Organization and the United Nations Children’s Fund recommend exclusive breastfeeding until 6 months of age [6]. Yet nationally representative data collected in 2010 showed that while more than 95 % of Western Australian (WA) mothers initiated breastfeeding only 58 % were exclusively breastfeeding to 1 month of age and 15 % of infants were exclusively breastfed to 6 months of age [7]. Locally collected data show these rates have remained relatively unchanged for the past two decades amongst women in Perth, WA [8–10].

The decisions to breastfeed and to continue breastfeeding are influenced by a complex variety of inter-related socio-demographic, psychosocial, biomedical and environmental factors [11]. Social support for breastfeeding from a woman’s partner, family and friends has been implicated as an important factor that influences the choice and duration of breastfeeding. In Western societies in particular, there is strong evidence that fathers influence the initiation of breastfeeding [12–14], contribute to maternal breastfeeding confidence [15–18], impact decisions regarding duration and weaning [19, 20] and that without their partner’s support mothers are more likely to breastfeed for a shorter duration [21–23]. Research indicates that the support of fathers is critical to breastfeeding success and is identified as one of the strongest and most consistent factors associated with women’s willingness to breastfeed [24].

Although fathers typically describe breastfeeding as being normal and natural and can readily recite the ‘Breast is Best’ mantra, they are often poorly informed about the importance of breastfeeding and its non-equivalence with formula feeding [25]. In addition, they can hold negative attitudes regarding breastfeeding including feeling left out and fear of losing time with, and the attention of, their partner [22, 26, 27]. This highlights the need for fathers to be included in the antenatal preparation for breastfeeding [28] as well as in the postnatal period, so as to deflect negative attitudes associated with breastfeeding and increase support for the mother [29]. Furthermore, fathers want to be involved in the breastfeeding decision making process [26] and new fathers want practical advice on how they can support their partner as well as strategies for troubleshooting/problem solving common breastfeeding difficulties that their partner may encounter [30]. Fathers need to identify and fulfil their unique role in ensuring their infants receive the benefits of breastfeeding by using their knowledge and skills to assist and support their partner [29]. By involving both the mother and father in infant feeding discussions and processes, it is predicted parents will adopt more positive breastfeeding behaviours [28, 31].

While the importance of the emotional and practical support provided by a woman’s partner to her breastfeeding success is well recognised, and the involvement of fathers in breastfeeding interventions routinely called for [32], relatively few interventions have targeted fathers and have been designed to allow rigorous evaluation. A recent systematic review investigating the impact of male-partner-focused interventions on breastfeeding outcomes identified only four studies published prior to January 2012 which had used either a randomised controlled trial (RCT) or quasi experimental design [33]. Since this time, the results of a quasi-experimental study targeting couples in Viet Nam [34] and a Canadian RCT also targeting couples have been reported [35]. In addition, we have published the results of the Fathers Infant Feeding Initiative (FIFI) one of the largest (n = 700) father-focused RCT conducted to date and the first conducted in Australia [36]. FIFI and other experimental studies have been successful in increasing breastfeeding initiation rates [14, 37] and higher rates of breastfeeding in the short-term (e.g. at 6 weeks) [36, 37] amongst the intervention group but only three studies have had a significant impact on duration of exclusive breastfeeding to four [38] or six [34, 39] months. All these interventions involving fathers provided breastfeeding education classes for fathers and therefore provide sufficient empirical evidence to justify the incorporation of education sessions for fathers into the routine antenatal education program.

Our earlier intervention, the FIFI study, resulted in increased rates of any breastfeeding at six weeks but failed to result in an increase in the proportion of couples fully or exclusively breastfeeding at this time and there was no difference between intervention and control couples in the proportion still breastfeeding at six months [36]. A limitation of this earlier intervention was that it only ran for six weeks and was of relatively low intensity, involving a breastfeeding focussed antenatal education for fathers led by a male facilitator, followed by the weekly delivery of printed educational and promotional materials to six weeks postpartum.

### Aim and objectives

The aim of the PIFI study is to build on the lessons learned from the exploratory FIFI efficacy study and to design, deliver and evaluate three interventions of differing intensity and duration targeted at couples but channelled through the male partner. The main focus of the PIFI study is to prolong breastfeeding duration, and in particular the duration of exclusive breastfeeding.

#### Primary objective

To measure the effectiveness of each of three interventions designed to increase the duration of breastfeeding among new parents in urban areas.

#### Secondary objective

To determine the cost-effectiveness of each intervention.

#### Study hypotheses

It is anticipated that the intervention will result in*H1*: a 10 % or greater difference between the interventions and control groups in the proportion of mothers who are breastfeeding at six weeks and six months;*H2:* a 10 % or greater difference between the interventions and control groups in the proportion of mothers who introduce infant formula and complementary food during the first six months after birth.

## Methods/design

### Study design

The Parent Infant Feeding Initiative (PIFI) is a four arm, factorial, randomised controlled trial. The study is registered with the Australian New Zealand Clinical Trials Registry (ACTRN:12614000605695, Universal Trial No.:U1111-1155-7115). Reporting of the study will adhere to the Consolidated Standards of Reporting Trials (CONSORT) guidelines for reporting parallel group randomised trials [40].

The trial arms will consist of a control, two medium and one high level intervention groups (see Fig. 1). The *Control Group (CG)* will have access to the usual antenatal and postnatal services provided by the hospital. The *Medium Intensity Intervention 1 (MI1)* will consist of a specialised antenatal breastfeeding education session delivered to the fathers, plus associated take-home educational print material for both parents. In the *Medium Intensity Intervention 2* (*MI2*), the social support intervention will be delivered directly to the father via a smartphone application antenatally from time of recruitment until 26 weeks postnatally. The *High Intensity Intervention* (*HI*) will include both the specialised antenatal class and the social support intervention.

**Fig. 1 Fig1:**
[figure not shown]
Intervention design

### Setting

Participants will be recruited from selected public and private hospitals with maternity departments in Perth, Western Australia.

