### Recruitment

Recruitment will take approximately 18 months, allowing for a wash-out period between each intervention arm in each hospital. The *MI1* and *HI* being hospital-based require access to antenatal classes. Usually antenatal classes run for a month and there is little overlap between classes. Each hospital has a series of antenatal classes and most metropolitan hospitals have at least 2 classes per week occurring on different days. As the researchers will be conducting the special antenatal classes and as the social support intervention happens externally to the hospital we are confident that there will be no leakage between intervention and control participants. Nevertheless, to ensure there is no contamination a washout period will be incorporated in the *MI1* and *HI* interventions.

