The Control Group *(CG)* will receive the standard breastfeeding support which will include information provided by hospital antenatal education programs and in-hospital breastfeeding support. All parents will be free to attend other antenatal classes or seek other breastfeeding assistance from the community. Uptake of these additional activities will be measured via the postnatal six and 26 week surveys.

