### Randomisation

Randomisation will be determined through a computer-based random sequence generator. Participants will not be blinded to the true nature of the study, nor will researchers be blinded to participants’ group allocation, however the study statistician will analyse the data independently and hence will be blinded to the allocation of participants to groups.

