### Ethical considerations

Participants will be provided with verbal and written information describing the purpose of the intervention and what their participation will involve. They will be advised that they may decline to participate without prejudice. Written informed consent will be obtained from both partners prior to randomisation into a study arm. They will be assigned a unique ID number which will link partners and their baseline and follow-up questionnaires.

When agreeing to participate in the study participants will be assured of anonymity and confidentiality. They will be requested to provide their name, address, email and phone number so that they can be followed-up by phone call, short message service (SMS) and email. Any woman who declines to participate in the study will be requested to anonymously provide basic demographic information, including age, years of education, marital status and intended method of feeding. It will be explained that this basic information will be used only to determine if the final sample is representative of new mothers and fathers in general. The right of non-participants to decline to provide this information will be respected.

The project has been approved by the Curtin University Human Research Ethics Committee (HR 82/2014; 14 May 2014) and the Human Research Ethics Committees responsible for the public (SCGG HREC No 2014–111; 18 Sept 2014) and private (SJGHC Ref: 777; 8 April 2015) hospital sites.

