### Statistical considerations

#### Sample size

The key outcome variable for statistical analysis is duration of breastfeeding. It is assumed that at 26 weeks, there is at least a 10 % difference in the proportion of mothers’ breastfeeding between any two of the groups. A sample size of 300 participants (fathers) is required in each of the 3 intervention groups and control group to be able to detect the difference at 80 % power and 5 % level of significance, using a Log-rank survival test. Assuming a loss to follow-up of 25 % in each group, a total of 400 participants for each group will be recruited (Total n recruited = 1600 couples, total n required =1200). The sample size was calculated in terms of the hazard ratio taking into account the censoring of data, as survival analysis will be used for the analysis of time to breastfeeding cessation, the main outcome variable.

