Multivariable survival and logistic regression analyses will be used to assess the effect of the treatment groups on the outcome after adjusting for covariates. The study has a factorial treatment structure comparing Antenatal Education (Yes, No) and Social Support (Yes, No). In addition to testing the main effects, this factorial treatment structure will allow the testing of the interaction between any two factors. It is hypothesised that the combined effect of both interventions will be significantly greater than the effect of either intervention in isolation. The main effects of antenatal education and social support together with all the interactions between these factors will be assessed in the analyses of the data. Survival analysis will be used to examine the effects of the various treatment groups on the duration of any and exclusive breastfeeding. A similar analysis will be performed for introduction of infant formula and complementary food. This type of analysis allows for the presence of censored data. ‘Censored data’ refers to those cases where breastfeeding continues beyond the end of the study period or beyond the time at which the subject dropped out of the study. Variables reported in the literature to be associated with duration of overall breastfeeding and age of introduction of complementary foods will be investigated using Cox’s proportional hazards model. This model allows joint estimation of the effects of predictor variables on the ‘hazard’ – *the risk of cessation of breastfeeding/complementary food introduction*. Possible covariates that will be considered in the Survival analysis will include amongst others: socio-demographic factors such as maternal age, level of education and return to work; biomedical factors such as parity, maternal smoking and weight status; and psychosocial factors such as infant feeding attitudes, breastfeeding self-efficacy, parental stress and anxiety.

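### Recruiting hospital defines usual care, but the stated randomisation, log-rank test and named covariates do not commit the trial to accounting for it: a modest loss of precision, not a bias

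*Protocol article*

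**What the plan says.** All references are to the protocol article.

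- **Setting:** "Participants will be recruited from selected public and private hospitals with maternity departments in Perth, Western Australia".
- **Study design:** the control group "will have access to the usual antenatal and postnatal services provided by the hospital". **The interventions** describes this as "information provided by hospital antenatal education programs and in-hospital breastfeeding support". What a control couple receives therefore depends on the hospital.
- **Randomisation:** "Randomisation will be determined through a computer-based random sequence generator". No stratification factor is mentioned. **Ethical considerations** adds "Written informed consent will be obtained from both partners prior to randomisation into a study arm".
- **Recruitment:** about 18 months, "allowing for a wash-out period between each intervention arm in each hospital".
- **Sample size:** 300 per group for 80% power at the 5% level to detect a 10-point difference at 26 weeks, "using a Log-rank survival test". No strata are mentioned.
- **Data analyses:** multivariable survival and logistic regression with covariate adjustment. The candidates are socio-demographic (maternal age, education, return to work), "biomedical factors such as parity, maternal smoking and weight status", and psychosocial. Neither hospital nor public/private status is named. The list is introduced as possible covariates and is expressly not exhaustive.

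**The concern.** Hospital could affect breastfeeding duration in two ways: through the families it serves and through the usual care it gives. It is fixed before randomisation and cannot be missing. The article names candidate covariates down to smoking and weight status, and includes return to work, which is settled after randomisation. It does not say that hospital will be used.

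Two things are at stake.

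- **Power.** Pooling hospitals with different cessation rates in an unstratified time-to-event comparison pulls the hazard ratio towards 1, and the trial is planned at exactly 80% power.
- **Protection against imbalance.** If the arms end up with different hospital mixes, an analysis that ignores hospital carries that difference into the estimate.

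**Working it through.** **The plan's own figure.** 300 / (1 − 0.25) = 400 per group, and 4 × 400 = 1600, as stated. The 300 cannot be checked uniquely, because the article gives neither a control rate nor a hazard ratio. With HR = ln(p + 0.10)/ln(p) and a two-sided 5% level, Schoenfeld/Freedman give 291/295 per arm at 25% v 35% and 376/382 at 50% v 60%. So 300 is attainable under some assumptions and is not shown to be wrong.

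**Inputs.** From the article: 300 per arm, 26 weeks, log-rank test, 5% level (two-sided assumed). Assumed: the hospital rates, the number of hospitals, exponential cessation times and the hazard ratio.

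**Power, two hospital types.** Half of couples in each type, HR 0.70 within type, 4000 simulated trials per scenario, censoring at 26 weeks. Each scenario was run twice.

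| Control rate at 26 weeks, by type | Gap | Unstratified v stratified, run 1 | Run 2 |
|---|---|---|---|
| 40% / 60% | 20 points | 81.7% v 83.2% | 81% v 82% |
| 35% / 65% | 30 points | 78.8% v 82.9% | 79% v 82% |
| 30% / 70% | 40 points | 74.8% v 82.7% | 76% v 82% |

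The standard error of each simulated power is about √(0.8 × 0.2 / 4000) = 0.6 points. A further repeat put the gains at about 2, 3 and 7 points.

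HR 0.70 is slightly larger than the planned effect. At 40%/60% it gives (0.40^0.7 + 0.60^0.7)/2 = (0.527 + 0.699)/2 = 0.613 against 0.50, or about 11 points rather than 10.

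**Power, six hospitals.** Equal-sized hospitals, average control rate 50%, overall difference set to exactly 10 points, 3000 trials per scenario.

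| Range of hospital rates | Unstratified | Stratified | Gain | Unstratified type I error |
|---|---|---|---|---|
| 40–60% | 71.6% | 71.7% | 0.1 | 5.3% |
| 30–70% | 71.7% | 74.7% | 3.0 | 4.6% |
| 20–80% | 71.1% | 79.6% | 8.5 | 4.6% |

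The type I errors have a standard error of about √(0.05 × 0.95 / 3000) = 0.4 points, so all three are compatible with 5%.

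**Chance imbalance.** With half of couples in private hospitals, the SD of the difference in private share between two arms of 300 is √(2 × 0.25 / 300) = 0.041, or 4.1 points. The shift in the 26-week difference is the imbalance multiplied by the gap in rates. For a 1-SD imbalance it is 0.041 × 20 = 0.8 points at a 20-point gap and 0.041 × 40 = 1.6 points at a 40-point gap.

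**Larger, imposed imbalance.** No true effect, 40%/60%:

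- 10 points: shift 0.10 × 20 = 2 points; type I error about 7% unstratified v 5% stratified.
- 20 points: shift 0.20 × 20 = 4 points; type I error about 17% v 5%.

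These error rates are conditional on the imbalance. By chance, 10 points is 10/4.1 = 2.4 SD (probability about 1.4%) and 20 points is 20/4.1 = 4.9 SD (about one in a million).

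**The case against.** The case against has several parts.

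- **This is a condensed article, and the covariate list is open.** Nothing in the text excludes strata or hospital adjustment, and the full plan may contain both. This stands: the article cannot be read as leaving hospital out. The remaining point is that it fixes a test and names candidates without committing to a factor that is complete and known before allocation.
- **The log-rank test is named only for the sample size.** The planned analysis is covariate-adjusted regression. Age, education, parity, smoking and the psychosocial scores may absorb part of the difference between hospitals' families. This stands in part: the simulations compare unadjusted tests, so the gain over a well-adjusted Cox model could be smaller. Those covariates do not capture differences in the hospitals' own usual care.
- **Randomisation balances hospital in expectation.** This stands, and it settles the bias question for individual, concurrent allocation.

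A reader might infer that hospital differences bias the comparison or push type I error to 7% or 17%. The documents do not support that: those figures need imbalances that chance would rarely or almost never produce.

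A reader might also point to the ethics approvals in Ethical considerations (public sites 18 September 2014, private sites 8 April 2015) as showing a shifting hospital mix. If the arms run at the same time, a shift affects all of them alike. It would matter only if the wash-out between arms in each hospital, described under Recruitment, means that arms run in blocks. The article does not say so, and such blocks would sit awkwardly with consent before randomisation and a random sequence.

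**Conclusion.** The point holds as one about precision and about protection against imbalance that actually occurs. The article recruits across public and private hospitals, lets the hospital define usual care, and does not commit to accounting for hospital.

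At 300 per arm the cost is about 2 to 7 points of power if two hospital types differ by 20 to 40 points at 26 weeks. With rates spread over six hospitals it ranges from nearly nothing (40–60%) to 8.5 points (20–80%). All of these rates are assumptions.

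Under individual, concurrent randomisation there is no systematic bias and no type I error inflation. Imbalance beyond chance becomes a concern only if the arms run in blocks within hospitals. In that case clustering and calendar time would also matter, and stratifying by hospital would not resolve either of them.

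**What to change.** In Data analyses, prespecify recruiting hospital as a stratum in the log-rank test and the Cox models, and as a fixed covariate in the logistic models. Hospitals with very few couples are merged by type (public or private). In Randomisation, state whether the sequence is generated separately within each hospital, and do so if the allocation lists are not yet final. State under Recruitment whether the arms run concurrently within each hospital or in blocks.

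The cost is a sentence in each place and no new data. The downside is a negligible loss of information from sparse strata, which merging limits. The change should be made before outcome data are seen.
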